## Abstract

**Background:**

Borderline Personality Disorder (BPD) is a serious mental disorder. Mentalization-based treatment (MBT) is an evidence-based treatment for individuals with BPD. Specifically, MBT has previously been highlighted for its effectiveness regarding the reduction of suicidal and non-suicidal self-injury (NSSI). Yet, randomized-controlled trials (RCT) on MBT in outpatient settings compared with bona fide treatment (BFT) are still scarce and none has been conducted in Germany. The primary objective of this RCT is to investigate whether outpatient MBT is more effective in the reduction of crisis events (incidences of NSSI and suicide attempts) compared with BFT (namely psychodynamic or cognitive-behavioural psychotherapy) in Germany. Secondary, MBT’s efficacy will be investigated with regard to cost-effectiveness within the German health care system, general and interpersonal functioning, BPD and general symptom severity, social adjustment, quality of life, reduction in psychotropic medication and therapy retention. Additionally, moderator as well as common and treatment specific mediator variables will be investigated.

**Methods:**

Across 5 study sites in Germany, 304 individuals of all genders from age 18 to 65 with a BPD diagnosis and NSSI or suicide attempts in the past will be asked to participate in the study for a period of two years. In the first year, patients will receive either MBT or BFT and will take part in continuous scientific assessments. Scientific assessments will continue after therapy completion up to a 12-month follow up. As primary outcome, crisis events will be assessed via ecological momentary assessment (EMA) in one week per month (four weekly assessments) during the first year, and in one week every three months during the second year. Number of crisis events up to 2 years post randomization will be compared between treatment arms using a log-linear regression model following an intention-to-treat approach. Secondary outcomes and mediator variables will be assessed at several timepoints.

**Discussion:**

This study investigates efficacy of MBT as BPD specific treatment in an outpatient setting compared with BFT in Germany. Results of this study can address a treatment gap in the German healthcare system, and inform about health economic aspects of BPD treatment as well as mechanisms of psychotherapeutic change.

**Trial registration:**

NCT06018272, https://www.clinicaltrials.gov/, August 30, 2023.

**Supplementary Information:**

The online version contains supplementary material available at 10.1186/s12888-025-06809-0.

## Background

Borderline Personality Disorder (BPD) is a severe mental health disorder characterized by at least five of the following nine criteria according to DSM- 5, section II (DSM, [1]): unstable relationships, inappropriate anger, frantic effort to avoid abandonment, affective instability, impulsivity, self-harm/suicidality, dysphoria, stress-related paranoid thoughts, and identity disturbance and dissociation. BPD is the only categorical qualifier that will remain in the new personality disorder classification of the ICD- 11 [2]. Point prevalence in community samples is around 2% [3], lifetime prevalence is around 6% [4]. BPD is the most common personality disorder in clinical populations, with prevalence rates of around 10% in outpatient and 15–25% in inpatient settings [5]. BPD is often associated with comorbid DSM-IV axis I and II disorders: approximately 85% of BPD patients have a 12-months diagnosis of at least one axis I and 74% for another axis II disorder [6]. Sixty-nine to 80% of BPD patients engage in suicidal behaviour and 3–10% commit suicide with a 50-fold heightened risk in comparison to the general population [6–8]. Up to 50% of BPD patients show co-occurring conditions of Post-Traumatic-Stress-Disorder (PTSD) which can be captured by a new diagnosis in ICD- 11 termed “complex PTSD” [9]. BPD accounts for 2.2% of all disability adjusted life years (DALYs) (ranking 3rd in mental disorders in women, and 4 th in men) and suicide accounts for 1.0–2.8% of all DALYs [10]. Furthermore, patients with BPD between the ages of 20 and 50 years have a mortality rate on average 2.30 times higher than the normal population and a loss of life years of between 6.8 and 9.3 years [11]. Studies on the economic burden of BPD on society diverge in their exact numbers due to different cost calculations, either pointing out a main relevance of indirect costs (76.3% of total costs of BPD) or equal relevance of indirect and direct costs [12]. Yet, studies concur in their findings that the economic burden of BPD is strikingly high compared with other psychiatric disorders (e.g. depression or alcohol abuse) with the main driver of direct costs being costs for hospital stays, and the main driver of indirect costs being productivity losses due to disability [12].

Mentalization-based treatment (MBT, [13]) has specifically been developed for the treatment of individuals with BPD. MBT is an integrative psychodynamic treatment rooted in attachment theory [14]. It assumes that mentalizing vulnerabilities lie at the core of the disorder. Mentalizing is the imaginative ability to interpret and understand the behaviour of oneself and of others in terms of mental states and develops in early attachment relationships [15]. Empirical research has shown that mentalizing is highly impaired in individuals with BPD especially with regard to emotionally intense relationships [14]. MBT follows distinct therapy rationales and is assumed to help alleviate BPD symptoms through inter alia improving mentalizing and epistemic trust, i.e. the trust in interpersonally transmitted information being relevant, trustworthy and generalizable for the individual [16]. MBT, alongside dialectical behaviour therapy (DBT; [17]), is the most studied psychotherapy for BPD. Five randomized-controlled trials (RCTs) have investigated the efficacy of MBT in BPD in comparison to psychiatric services [18], structured clinical services including supportive psychotherapy [19, 20], specialist BFT [21] and in adolescents with non-suicidal self-injury (NSSI) who mainly fulfilled criteria for BPD [22]. MBT proved to be superior to bona fide treatment (BFT)/clinical management in NSSI, suicide attempts, psychiatric symptoms, and hospitalization [18, 22] as well as core BPD symptoms [22, 23]. One RCT found MBT as effective as a specialist treatment-as-usual (TAU) for the primary outcome, reduction of Borderline symptom severity, with large effect sizes for both groups; however, there were significantly fewer drop-outs in the MBT group [21]. One independent RCT confirmed positive effects for MBT in comparison to supportive therapy for general functioning and BPD symptoms, suggesting that MBT may address core problems in BPD beyond NSSI and suicidality [20]. MBT is the only treatment for which superiority to clinical management was demonstrated in all primary outcome variables as well as a significantly higher level of employment or academic/occupation training eight years after randomization [24]. Findings also demonstrate that MBT shows superiority over TAU for interpersonal problems and general functioning [25]. In sum, MBT has demonstrated reliable improvements for psychiatric symptoms.

Although the most recent Cochrane review lists MBT as evidence-based treatment for BPD and highlights its effectiveness in treating NSSI and suicidality [26], quality of evidence for efficacy of BPD specific treatments is still rated low indicating the need for further studies. Also reviews and meta-analyses conclude that there is strong need for confirmatory trials with high study quality and sufficient sample sizes [8, 25, 27], cost-effectiveness studies [27] and the inclusion of quality of life and preference measures [25]. McLaughlin et al. [28] and Oud et al. [27] also recommend to investigate the effective ingredients in treatments. Furthermore, although MBT has increasingly been clinically implemented in several German inpatient units as well as in outpatient treatment, its efficacy has not yet been studied in Germany.

## Methods/design

### Aim, design and setting

Based on the above-mentioned observations, we designed this cluster-randomized controlled trial (cRCT). It will be the first in Germany to investigate the efficacy of an outpatient MBT in comparison to BFT (here psychodynamic psychotherapy, PT, or cognitive-behavioural psychotherapy, CBT) for patients with BPD. BFT was chosen as a comparator for reasons of ecological validity. The primary objective of the RCT is to investigate whether MBT is more effective in the reduction of crisis events compared to BFT. Secondary, the trial will investigate whether MBT is superior to BFT with regard to cost-effectiveness, general and interpersonal functioning, BPD and psychiatric symptom severity, social adjustment, quality of life, changes in psychotropic medication and therapy retention. We expect that MBT will prove superior to BFT in all primary and secondary endpoints. We expect MBT to be more cost-effective for estimates on the financial burden of patients on society. Finally, while there are theories about and preliminary evidence for mechanisms of change [29], empirical validation of these mechanisms is lacking [30]. Thus, this trial will investigate moderator and mediator variables potentially associated with treatment outcome. Moderator variables are pre-treatment variables that predict treatment outcome in MBT and BFT (e.g. severity of BPD, treatment preferences, gender, trauma, initial level of mentalization and attachment). Mediator variables, i.e. the process of change, will be investigated comparing similarities and differences in change patterns between MBT and BFT. This is done by tracking changes of common and specific treatment factors in response to various stimuli. Common factors tracked are therapeutic alliance from both perspectives (patient and therapist) and both settings (individual and group) [31] as well as therapy related agency [32]. Specific factors are changes in mentalizing [33], epistemic trust [34], emotion regulation [35], attachment [36, 37], social pain (e. g. emotional reactions to rejection) [38], automatic thoughts [39], as well as therapist variables (treatment adherence and competence; [40, 41], and therapist-patient verbal and non-verbal interaction (attunement, [42]; rupture-resolution [43]).

To investigate efficacy of MBT versus BFT, a total of *n* = 544 patients with a BPD diagnosis will be screened for eligibility at five study sites in Germany: University Hospital Heidelberg (Institute for Psychosocial Prevention, ST, and Department of General Psychiatry, SHe), University Hospital Jena (Institute for Psychosocial Medicine, Psychotherapy and Psychooncology, BS), University Hospital Düsseldorf (Clinic for Psychosomatic Medicine and Psychotherapy, UDE & JR), University Hospital Ulm (Clinic for Psychosomatic Medicine and Psychotherapy, HG, JV), Psychologische Hochschule Berlin (Department of Clinical Psychology and Psychotherapy, TS). Of the patients screened, *n* = 304 are expected to fulfil all inclusion criteria including informed consent to participate in the trial, to complete the baseline assessment (T0) and to be allocated to the trial (Fig. 1). Patients will be randomized in groups of 8 (randomization cluster) in a 1:1 ratio to either MBT or BFT using block randomization. Randomization will be stratified by study site. For randomization, study site coordinators will use a centralized web-based tool (randomizer.at) to maintain allocation concealment. Role-based user rights ensure that only approved study personnel may perform randomizations. Main assessments will be conducted for both arms at 6 months (in-therapy assessment, T1), at 12 months (T2) and at 24 months after start of therapy (12-months follow-up, T3). A final sample of *n* = 304 is expected to be obtained for data clearance and analysis using an intent-to-treat protocol. A drop-out of 30% during therapy is expected and acknowledged in our power analysis. Blinding of study team, trial personnel at site as well as patients is not feasible due to the nature of the interventions. Only central assessors will be blind to treatment. Allegiance bias is minimized as the consortium includes representatives of all trial treatments (MBT, group therapy, BFT).

**Fig. 1 Fig1:**
[figure not shown]
Study flow-chart. Sequence of steps from eligibility assessment to data analysis in both settings

## Participants

Individuals with a BPD diagnosis (ICD- 10: F60.3; DSM- 5: 301.83, ICD- 11: Borderline qualifier) of all genders will be included if they are between 18 and 65 years old and report NSSI or suicide attempts in the past two years as indicated by the International Personality Disorders Examination (IPDE) [44] item “repeated suicidal behaviours, gestures, threats or self-harm”, one of which has to have occurred within the past six months. The informed consent will be obtained in person by the clinicians that carry out the diagnostic assessments. Key exclusion criteria are moderate and severe acute substance use disorder (exception: cannabis use), a diagnosis of schizophrenia or schizotypal personality disorder, bipolar I disorder (DSM- 5), cognitive impairment (IQ < 80 measured with Raven’s progressive matrices (RPM- 2; [45]) in case of suspicion of intellectual disability) or evidence of organic brain disorder, BMI < 16.5, a serious medical condition that will require hospitalization within the next year (e.g., cancer) and no sufficient German language abilities. We do not exclude patients with a broad range of co-morbidities and medication to provide the best possible generalizability to the population of BPD patients in Germany. Patients who require inpatient treatment during psychotherapy, with a stay lasting longer than 4 weeks, are excluded from the study and counted as drop-outs.

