## Additional treatments

Additional treatments except concomitant psychotherapy (including inpatient psychotherapy > 4 weeks) will be allowed in the two arms of the trial. Additional treatment can comprise pharmacotherapy, rescue medication, self-help groups, managed care, crisis interventions in psychiatry. Most trials in BPD so far have allowed concurrent psychotropic treatments [25] which reflects the use of pharmacotherapy in BPD [46]. All additional treatments will be systematically assessed and controlled for in data analysis. Changes in psychotropic treatment are measured as a secondary outcome.

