### Compliance/rate of loss to follow-up

Building on similar trials comparing MBT with BFT for BPD patients we expect a compliance rate of about 70%, with Bateman and colleagues [19] achieving 99/134 = 73% compliance over 18 months and Jorgensen and colleagues achieving 63/85 = 74% compliance over 24 months [20]. Both Poisson regression for analyzing the primary outcome and multilevel models for analyzing the secondary outcomes handle unbalanced data with different number of measurements per person [115]. As such, the intent-to-treat sample is used in all analyses instead of complete cases.

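### Excluding patients from the study for an inpatient stay over 4 weeks ends follow-up on an event plausibly tied to outcome and cost; stopping therapy and leaving the study should be separated

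*Protocol article*

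**What the plan says.** The rule stands under Participants: "Patients who require inpatient treatment during psychotherapy, with a stay lasting longer than 4 weeks, are excluded from the study and counted as drop-outs". It concerns patients already in therapy, so already randomised, and it speaks of the study, not only of the study therapy.

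The inpatient rule is worded differently under Additional treatments: "Additional treatments except concomitant psychotherapy (including inpatient psychotherapy > 4 weeks) will be allowed in the two arms of the trial". The next sentence there adds: "Additional treatment can comprise pharmacotherapy, rescue medication, self-help groups, managed care, crisis interventions in psychiatry". No length limit is attached to psychiatric crisis care.

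On the analysis population, Aim, design and setting states: "A final sample of *n* = 304 is expected to be obtained for data clearance and analysis using an intent-to-treat protocol". Compliance/rate of loss to follow-up adds: "As such, the intent-to-treat sample is used in all analyses instead of complete cases". The Abstract promises an intention-to-treat comparison of events up to 2 years after randomisation. Primary analysis counts events through therapy and the following 12 months, with log observation time as offset. It fills missing values by multiple imputation on randomisation cluster, sex, age and the variable's own values over time.

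On costs, the Background describes the economic burden "with the main driver of direct costs being costs for hospital stays". The Discussion says that frequent crisis events may be one reason why so many inpatients have this disorder.

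**The concern.** A patient who leaves the study at admission contributes no later EMA weeks, no later T1 to T3 assessment and no later service-use schedule (AD-SUS). That is the natural reading of exclusion from the study, and no section says otherwise. Suicides enter the primary outcome through SAE reports, and the article does not say that these continue after exclusion.

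This loss is imposed by the protocol, and its trigger is plausibly related to the primary outcome. If long stays are commoner in one arm, high-rate follow-up time is lost unevenly and the rate ratio shifts. The cost-effectiveness analysis is also exposed: the AD-SUS at the next assessment would have captured the long stay and what followed, and that form may never be completed. An analysis plan cannot recover data that were not collected.

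The period at risk of removal can also differ by arm, because the rule applies only while psychotherapy is running, and site staff and patients are not blinded.

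**Working it through.** **Plan's own figure.** Inputs from Power calculations and sample size: 5 against 3.75 events, ratio 0.75, 38 clusters of 8 (152 patients per arm), ICC 0.1, drop-out 30% with a squared correction, two-sided 0.05.

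- Effective n per arm = 152 × 0.7² / (1 + 7 × 0.1) = 43.8.
- SE of the log ratio = √[(1/5 + 1/3.75)/43.8] = 0.103.
- Power = Φ(0.2877/0.103 − 1.96) = 0.796, against a stated 78%.

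The stated power therefore reproduces closely. The issue is bias, not sample size.

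**Illustration of the bias.** The article gives no rate of stays over 4 weeks, so everything in this step except the ratio of 0.75 is an assumption. Let p be the share with a long stay, m their event rate relative to other patients in the same arm, and removal occur at month t = 6 of 24. No imputation is applied.

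- Full-follow-up mean per arm, relative to patients without a long stay: F(p) = (1 − p) + pm.
- Observed rate with the time offset: O(p) = [(1 − p)·24 + p·m·t] / [(1 − p)·24 + p·t].
- Hold the overall true ratio at 0.75. The ratio within each group of patients is then w = 0.75 / [F(MBT)/F(BFT)], and the estimate is w × O(MBT)/O(BFT).

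Scenario A, 10% BFT and 5% MBT, m = 3:
- F ratio = 1.10/1.20 = 0.917, so w = 0.75/0.917 = 0.818.
- O(MBT) = 23.7/23.1 = 1.026; O(BFT) = 23.4/22.2 = 1.054; ratio 0.973.
- Estimate = 0.818 × 0.973 = 0.80. Share of the log effect lost = 1 − ln 0.796/ln 0.75 = 21%.

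Scenario B, 15% BFT and 8% MBT, m = 5:
- F ratio = 1.32/1.60 = 0.825, so w = 0.909.
- O(MBT) = 24.48/22.56 = 1.085; O(BFT) = 24.9/21.3 = 1.169; ratio 0.928.
- Estimate = 0.909 × 0.928 = 0.84. Share of the log effect lost = 41%.

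Arms swapped (more long stays in MBT):
- A becomes (0.75 × 0.917)/0.973 = 0.71.
- B becomes (0.75 × 0.825)/0.928 = 0.67.

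With equal p in both arms, F and O cancel and the estimate stays at 0.75.

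**Second check by simulation.** True ratio 0.75, gamma-distributed patient rates (shape 1 or 0.5), removal risk proportional to the patient's rate, removal uniform over year 1, log-time offset, no imputation.

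| Removal BFT / MBT | Estimated ratio |
|---|---|
| 10% / 10% | about 0.75 |
| 20% / 10% | 0.83 to 0.88 |
| 10% / 20% | 0.63 to 0.68 |

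With equal removal the ratio holds, but the control rate falls from 5.0 to 4.6 (shape 1) or 4.2 (shape 0.5).

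**Window at risk.** MBT lasts 12 months. BFT runs from 12 to 100 hours at one or two sessions a week. Assuming one hour per session, that is 12/2 = 6 weeks to 100/1 = 100 weeks. The Procedure section puts the BFT average at 48 sessions, against a maximum of 58 in MBT, so the windows may be similar on average and differ mainly in spread.

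**The case against.** The strongest reply is that these patients are not lost to the analysis. They are counted as drop-outs; the article expects 30% drop-out during therapy and still expects 304 patients for analysis, with the intention-to-treat sample used in place of complete cases. Read together, this keeps them in the analysis set with data up to removal plus imputation. A reader might infer that the rule deletes them from the intention-to-treat set; the article does not support that. What stands is that their follow-up ends, and that the allowance for 30% drop-out protects power but does not remove bias.

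A reader might also infer that their missing values come only from patients without long stays. That is too strong, because the imputation uses the patient's own earlier values, which may recover part of the bias. The gap that remains is narrower: hospitalisation is not a listed variable, so a change in rate around admission is not captured.

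Nor is it shown that the removed patients have the worst outcomes. The Discussion links crises to inpatient care only as a possibility. On the wording under Additional treatments, the patients affected could be those receiving a competing inpatient psychotherapy, not those in crisis.

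On costs, stays of up to 4 weeks remain in the data, the Background statement is about hospital stays in general, and sensitivity analyses for protocol deviations are planned. Those analyses cannot replace data that were never collected.

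**Conclusion.** The point holds in this form: the rule as written ends observation of randomised patients on an event plausibly related to the primary outcome and to cost. That works against the stated intention-to-treat aim over 24 months, even if the patients stay in the analysis set. The offset and the imputation then treat the loss as uninformative.

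Direction and size are unknown. Under the assumptions above, with fewer long stays in MBT, 0.75 is estimated as about 0.80 or 0.84; with more, as about 0.71 or 0.67; with equal shares there is no shift. These figures ignore imputation and so lie towards the upper end.

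A reader might arrive at a far larger loss by supposing that the arms differ only in how often long stays occur. In scenario A the true ratio is then 0.917 and the estimate 0.973, a loss of 1 − ln 0.973/ln 0.917, about 69% of the log effect. Nothing in the article says that the whole treatment effect runs through long stays, so that figure should not be used.

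Confidence is high that the wording needs changing, and low about any particular size of bias.

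**What to change.** Amend the rule under Participants so that stopping study therapy and leaving the study are separate. All randomised patients are then followed to month 24 (EMA, T1 to T3, AD-SUS, SAE reports) unless they withdraw consent, and are analysed as randomised. Record the long stay as an intercurrent event handled by a treatment-policy strategy, and keep a version censored at the stay as a sensitivity analysis.

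Reconcile Participants, which covers any inpatient treatment over 4 weeks, with Additional treatments, which bars inpatient psychotherapy over 4 weeks and allows psychiatric crisis interventions. Which clinical rule should apply, and whether a patient continues study therapy, is not judged here.

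The cost is a protocol amendment and continued assessments for a minority of patients. Some power may be gained: with the formula above, loss of 25% in place of 30% would raise power from 0.796 to 0.848, although the article does not say how much of the 30% comes from this rule. Data not collected in the meantime cannot be recovered later.
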